### Shared Decision Making, Self-Monitoring, and Ecological Momentary Assessment

As the fields of mental health care and substance abuse treatment have changed, there has been a greater emphasis on the importance of patient autonomy and patient involvement in treatment. Active patient participation is a critical component of recovery and enhances the personal meaning, treatment satisfaction, and quality of life for the patient [12]. Shared decision making (SDM) is an interactive collaborative process between the health care provider and the patient in which the practitioner becomes a consultant to the patient, providing information, discussing options, and supporting the patient’s autonomy as they mutually decide on treatment options [13]. SDM has been found to be associated with improved outcomes in substance-dependent patients, including increased personal control and reduced drug use [14-15].

One important component of SUD treatment and prevention that contributes to patient autonomy is the use of self-monitoring logs, in which patients are directed to record details about their alcohol and drug use, including their moods and the situations in which use occurred. This practice serves multiple purposes—it provides an opportunity for the patients to talk openly and honestly about their alcohol and drug use, it encourages patients to take responsibility for their own behavior change, and it provides information that providers can use to observe patterns and give feedback about changes in alcohol and drug use over time [16]. Ecological momentary assessment (EMA) is a method in which data are collected in real-world environments as subjects go about their lives. Assessments focus on subjects’ current state based on strategically selected moments (eg, occasions when subjects have craving). In EMA, subjects complete multiple assessments over time, providing a picture of how their experiences and behavior vary over time and across situations [17].

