### Trial Process

#### Timing and Flow of the Randomized Controlled Trial

We will conduct an RCT with 500 patients with SUD risk in the UHD Clinic, a large academic primary care provider affiliated with a major public university. Recruited patients will be randomized into control and intervention arms. Both arms will take initial baseline and exit (30 days) surveys to evaluate self-reported substance use and specialty service utilization. The control arm patients will receive usual care. The intervention group patients will receive technology-enhanced SBIRT with a mobile follow-up program to track goals and substance use at home. The RCT will be managed by a team of seasoned SBIRT and addiction researchers and practitioners at the research site.

The RCT tracks participants for 30 days after the primary care encounter. We will collect feedback from the patients during the 30 days and count the number of patients who use specialty care services in specialty care programs for tobacco, alcohol, and drug abuse (both from self-reporting and from the service providers).

Since the clinical trial involves more than 9 human subjects, the RCT will be approved by the OMB as well as the university’s Institutional Review Board (IRB), which is responsible for research in the university affiliated health care providers. Figure 1 displays the flow of participants.

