#### Follow-Up

The control arm participants will receive no additional follow-up beyond usual care until the 30 days’ end.

The intervention arm participants will receive a once-per-day reminder to answer daily follow-up questions. The questionnaire screen includes:

Reminder for specialty care appointment the day before the appointment. The user can reschedule the appointment from the questionnaire screen. The questionnaire also asks whether the user went to the appointment on the day after.Adherence by participant to each of his or her own stated goals on that day.Using items from a drug use self-monitoring log developed by Sobell and Sobell [16], participants will be asked to report details of their drug and alcohol use within the last 24 hours, including drugs used, drinks had, cravings or urges to use drugs or drink alcohol, situations related to drug use (eg, patient was alone, in a social situation), and thoughts or feelings experienced when using drugs or during urges.

In the event of strong craving or substance use, the user is instructed to access an EMA screen bookmarked on his or her phone. The event-based EMA measures craving and surroundings at the time of craving or substance use.

Adapted from the 3-item Opioid Craving Scale by McHugh et al [31], participants will be asked to rate on a scale from 1 to 10 how much they currently crave a drug, how strong their desire to use has been when something in the environment reminded them of the drug, and the likelihood that they would use the drug in a specific environment.EMA items on psychological mood are adapted from an EMA assessment conducted by Gwaltney et al [32] and are designed to assess the participant’s affect state associated with substance use. The items ask participants to rate to what extent they feel happy, stressed, relaxed, bored, irritable, energized, and sleepy.

A risk score will be computed for every intervention participant every day. The score depends on the participant’s questionnaire adherence, self reported goal adherence, and substance use. If a participant is at high risk, he or she may be offered the brief intervention video to watch again.

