#### Exploratory Analysis

The exploratory analysis will be performed to gain further insights into additional data collected from the intervention participants. We will perform linear regression analysis to associate model technology acceptance factors with the participant’s inclination to adopt the technology in the future. This result will inform us on which factors are most important to patients for this tool. We will perform linear regression analysis to associate observed follow-up metrics such as ratio of missed questionnaires, substance use, and substance craving with participant referral decisions during the follow-up period. The result will inform a model to predict high-priority patients for referral in future interventions.

The association between mood and substance use and craving is inconclusive in existing research literature. In this project, we will collect self-reported mood and substance use/craving data from all intervention arm participants. We will group substance use/craving data into positive and negative mood categories and compare the differences using chi-square or *t* tests of the mean methods as appropriate. Furthermore, we can apply multilevel (also called mixed effect) regression models to EMA data. Mixed effects regression models can be applied to normally distributed continuous and categorical outcomes and nonnormally distributed outcomes such as counts with a Poisson distribution. Mixed effects models are also robust to missing data because time is treated as a continuous variable, the implication being that subjects are not assumed to have the same number of assessments at the same time points. To evaluate the relationship between craving, mood, and substance use, we used a generalized linear mixed model with a binary logistic response function of substance use. Fixed effects included craving for the substance and mood states.

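### The exploratory EMA logistic model does not separate person-level from momentary craving and mood, so its coefficients may mix two different associations

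*Protocol article*

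**What the plan says.** The Exploratory Analysis section of the protocol article proposes multilevel regression for the EMA data. The aim is worded generally: "To evaluate the relationship between craving, mood, and substance use". The model is then named, "we used a generalized linear mixed model with a binary logistic response function of substance use", and the predictors follow: "Fixed effects included craving for the substance and mood states". The section does not say how the ratings are coded, whether they are centred, how many terms each contributes, or which random effects are used. Its status is clear: "The exploratory analysis will be performed to gain further insights into additional data collected from the intervention participants".

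The Follow-Up section shows that the predictors are momentary. On craving, "participants will be asked to rate on a scale from 1 to 10 how much they currently crave a drug". On timing, "The event-based EMA measures craving and surroundings at the time of craving or substance use". Mood items belong to the same event-based assessment. In the Introduction, the section on shared decision making, self-monitoring and EMA describes repeated assessments as "providing a picture of how their experiences and behavior vary over time and across situations".

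**The concern.** A momentary craving rating can be high for two reasons: the participant generally craves more than others, or craving is above that participant's own usual level at that moment. The first gives a between-person association (people with more craving use more or less overall). The second gives a within-person association (use is more or less likely when a person's craving rises). These are different quantities and need not agree in size or sign.

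A logistic mixed model with one uncentred term per rating forces them to be equal. A random intercept does not undo this. The other mood analysis in the same section, which groups records by positive or negative mood and applies chi-square or t tests, does not separate people from moments either.

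What is at stake is interpretation. A between-person association could be found with one questionnaire per person, so the rationale for EMA points towards the within-person one. A mixed coefficient could be read as evidence that use follows rises in craving when it shows only that some people report more of both.

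**Working it through.** The article gives no figure for this model, so there is nothing to reproduce. The check is of the mechanism and its possible size.

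**1. The two models.** For participant i and record j, let x_ij be the rating, m_i the participant's mean rating and u_i the random intercept.

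- Single term: logit P(use_ij) = a + b·x_ij + u_i
- Split: logit P(use_ij) = a + b_W·(x_ij − m_i) + b_B·m_i + u_i

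Because x_ij = (x_ij − m_i) + m_i, the single-term model is the split model with b_W = b_B imposed. If the true slopes differ, the fitted b is a compromise, roughly (1 − w)·b_W + w·b_B with w between 0 and 1.

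**2. Inputs.** From the article: binary outcome, logistic link, intervention arm only, and "The RCT tracks participants for 30 days after the primary care encounter". With 500 participants, equal arms and 20% attrition (Power Calculation section), the arm has 250 × 0.8 = 200 people. Thirty records per person corresponds to one a day; 10 and 3 stand for sparser event-triggered reporting. Everything else is assumed: total craving variance 1 (slopes are log-odds per SD of craving, not per point of the 1 to 10 scale), half of it between people, intercept −0.5, random-intercept SD 1 (0.5 in the rows marked *), and the slopes.

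**3. Results.** Maximum likelihood with 40-point Gauss-Hermite quadrature, 20 runs per row. The last column is w = (b_W − b)/(b_W − b_B).

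| Records | True b_W | True b_B | Single slope b | Single slope significant | Split: within slope | w |
|---|---|---|---|---|---|---|
| 30 | 0 | 1 | 0.105 | 70% | 0.000 | 0.11 |
| 10 | 0 | 1 | 0.242 | 100% | −0.007 | 0.24 |
| 3 | 0 | 1 | 0.469 | 100% | 0.073 | 0.47 |
| 30 | 0.5 | −0.5 | 0.407 | 100% | 0.511 | 0.09 |
| 10 | 0.5 | −0.5 | 0.257 | 90% | 0.489 | 0.24 |
| 3 | 0.5 | −0.5 | 0.104 | 20% | 0.501 | 0.40 |
| 10* | 0.3 | −1 | −0.087 | 25% (negative) | 0.318 | 0.30 |
| 3* | 0.3 | −1 | −0.293 | 70% (negative) | 0.299 | 0.46 |
| 10 | 0.5 | 0.5 | 0.502 | 100% | 0.492 | none |

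**4. Reading.**

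- Rows 1 to 3: there is no within-person link, yet the single term gives odds ratios of exp(0.105) = 1.11, exp(0.242) = 1.27 and exp(0.469) = 1.60.
- Rows 4 to 6: a real within-person slope of 0.5 shrinks to 0.41, 0.26 and 0.10.
- Rows 7 and 8: the sign reverses, but only because the between-person slope is strong and of opposite sign.
- Row 9: with equal slopes there is no distortion.
- The distortion falls as records per person increase.

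**5. Precision.** The single slope varied between runs with an SD of about 0.05 to 0.14, so the averages have standard errors of about 0.05/√20 = 0.01 to 0.14/√20 = 0.03. The percentages are rough: for 70%, √(0.7 × 0.3/20) = 0.10. A separate set of 150 runs agrees. With about 10 records each, b_W = 0 and b_B = 0.8, the single term gave an odds ratio of 1.21, significant in about 81% of runs, and the split gave a within-person odds ratio of 1.01, significant in 5%. The weight in row 2 predicts exp(0.242 × 0.8) = 1.21.

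**The case against.** The strongest reply is that the article never says the ratings enter raw or as one term each. A model split into person mean and deviation also has craving and mood as fixed effects, and the word used for the list does not make it complete. A condensed article may leave such coding to a fuller document. A reader might infer that the plan commits to a single uncentred coefficient; the text does not go that far. What stands is narrower. The section states the outcome, link, model class and predictors, and someone following it as written would most naturally enter each rating as measured.

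Second, a within-person aim is not stated. The model's aim speaks only of a relationship, and the passage on variation over time is a general description of EMA in the Introduction. A reader might infer that the plan promises to settle the momentary question; it says only that the evidence on mood is unsettled and that these models can be applied. This too stands. The within-person interest is suggested by the reason for using EMA and is not fixed as an estimand.

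Third, the size is hypothetical. The daily log also asks about cravings, so up to 30 daily records are possible, though that is not the event-based craving scale. With 30 records the single slope lies closer to the within-person one (0.41 against 0.50; 0.11 against 0). That is fair, although the 0.11 was still significant in 70% of runs.

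**Conclusion.** The point holds as a conditional one. If the ratings enter as measured and the within-person and between-person slopes differ, the coefficients blend the two. They can suggest a momentary link that is absent or weaken one that is present. Under the assumed slopes of 0 within and 1 between, with half the craving variance between people, the single log-odds slope is about 0.11, 0.24 and 0.47 with 30, 10 and 3 records per person. Those inputs are not in the article, and the trial's own values could make the effect larger, smaller or nil.

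A reader might infer that the model is likely to report the wrong direction. The documents do not support that. Reversal needs slopes of opposite sign together with few records or a strong between-person slope. The familiar expectation that people who crave more also use more is a positive between-person slope, and blending it with a positive or zero within-person slope cannot produce a negative result.

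Priority is low. The analysis is exploratory and confined to the intervention arm. Neither primary hypothesis, none of the seven secondary hypotheses and no part of the randomised comparison depends on it.

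**What to change.** Enter each craving and mood rating as two fixed effects: the participant's own mean over follow-up, and the deviation of each record from that mean. Base any momentary (within-person) statement on the deviation term only. Report the person-mean term separately, labelled as a between-person association.

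The cost is one extra derived variable per predictor and a slightly wider interval for the within-person effect. No new data are needed. With few records the person mean is itself imprecise, so the between-person slope should be read with care. With 3 records and half the variance between people, the reliability of the mean is 0.5/(0.5 + 0.5/3) = 0.75. For true slopes of 0.5 within and −0.5 between, the expected person-mean coefficient is then about 0.75 × (−0.5) + 0.25 × 0.5 = −0.25 (simulated: −0.24). The deviation term does not have this problem. The split does not deal with any effect of recording craving only at triggered moments, which is a separate matter.

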#### Power Calculation

For primary hypothesis 1, we will perform a chi-square test to evaluate the difference in proportions of participants who receive specialty care in the 2 arms. We estimate that SBIRT intervention [37] could result in 10% to 30% of patients receiving specialty care. We computed power using the following assumptions: chi-square for 2 proportions, 2 samples, and 2-sided test; type 1 error rate of 5%; power of 0.9; control arm with 20% participants receiving specialty care; intervention arm with 35% participants receiving specialty care; and same number of participants in control and intervention. A sample of 197 participants in each of arms will be sufficiently powered to detect such differences between control and intervention arms.

For primary hypothesis 2, we assume that both arms start with the same levels of substance use. Therefore, to test the hypothesis, we will test the mean substance use levels at 30 days for both arms. We computed power for the sample *t* test of the mean using the following assumptions: 2-tailed *t* test for the mean of 2 samples; type 1 error rate of 5%; power of 0.9; medium Cohen effect size; and same number of participants in control and intervention. A sample of 86 participants in each arm will produce sufficient power. Based on the above calculation and considering up to 20% attrition, a sample of 500 total participants will have sufficient power to test both primary hypotheses.

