### Hypotheses

The RCT will address 2 primary hypotheses. Hypothesis 1 has 7 secondary hypotheses. Compared with the control group,

Significantly more intervention group patients will receive specialty SUD care within 30 days following the SBIRT encounter at the primary care clinic. The secondary hypotheses attempt to explain how and where the increased specialty care utilization occurs in the process.More intervention group patients are diagnosed with high-risk SUD.More intervention group patients are subsequently referred to specialty care at the end of the primary care clinic encounter.More intervention group patients are referred to specialty care during the 30-day following period due to failing to adhere to goals.Intervention group patients are more satisfied with the care they receive.Intervention group patients are more knowledgeable about SUD.Intervention group clinicians are more satisfied with the process.Intervention group clinicians spend less time on the SBIRT intervention and follow-up.Intervention group patients will report a greater reduction in substance use and a greater drop in Drug Abuse Screening Test (DAST-10) and Addiction Severity Index (ASI) scores within 30 days.

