#### Surveys

At the end of the primary care clinic visit, all participants will be asked to complete a survey about their experience with the process and their knowledge about SUDs. The intervention group patients will also be asked about their acceptance of the technology solution. The survey has the following components:

A 19-item validated computer system usability questionnaire is used to evaluate a computer system’s usability [33]. It also allows users to give free form answers on what he or she likes or dislikes about the system. We use it to evaluate the iPad tool in primary care clinics.A questionnaire based on the unified theory of acceptance and use of technology (UTAUT) by Venkatesh et al [34] is used to evaluate the technology solution’s ease-of-use, perceived usefulness, and the user’s social and facilitating conditions to predict the adoption of such technology solutions. The original UTAUT questions will be adapted to reflect our product.A 10-item validated patient satisfaction questionnaire will evaluate patient satisfaction with primary care providers [35].The ASI–Lite asks for drug use in the previous month, comorbid medical and mental illness, and social and legal outcomes related to drug use [36]. The ASI score is a quantitative measure of the user’s substance use.

At the end of the 30-day follow-up period, all participants will be asked to complete the screening, patient satisfaction, and ASI questionnaires again. They will also be asked to report any health care service they received during the 30 days, including any specialty SUD services. They can complete those questions on a computer or on paper. A complete schedule of all participant surveys and questionnaires is listed in Table 1.

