#### Hypotheses Testing

Since the hypotheses are primarily concerned about the observed differences between control and intervention arms, including referral rates, satisfaction level, knowledge level, and greater reduction in substance use, Student *t* tests will be used.

A chi-square test will be performed on the proportions of participants who receive specialty care to detect the significance in the difference between control and intervention arms. This test will be repeated for participants who have self-reported receiving specialty care. A chi-square test will be performed on the proportions of participants who receive specialty care referral at the end of the primary care encounter and who receive a specialty care referral during the 30-day follow-up period. For each question in the participant satisfaction survey and on the overall computed satisfaction and knowledge score, we will perform a *t* test for the answer’s mean value. Clinician interview results will be evaluated qualitatively to determine clinicians’ satisfaction with the solution.

Difference in differences regression tests will be performed on the differences in self-reported substance use amount and frequency and DAST-10 scores measured at baseline and 30 days of the study. The correlation coefficients and their confidence levels will be computed. These tests detect difference in drug use changes from control and intervention groups during the intervention period.

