## Results

In phase 1 of this project, we developed and piloted a prototype solution to enhance SBIRT in primary care office and follow up patients intensively for 30 days. The prototype proved feasibility of the technology, including the innovative user interface, dynamic screening logic, computerized brief intervention, shared-screen SDM, and bidirectional EMR connectivity. Our pilot clinicians and patients overwhelmingly determined the tool to be easy to use and not intrusive to normal clinical workflows. Patients with low-risk SUDs were also able to adhere to the shared goals during the follow-up period.

In phase 2 of this project, we supposed that, compared with the control group participants at 30 days, (1) significantly more intervention group patients will receive specialty SUD care and (2) intervention group patients will report a greater reduction in substance use and a greater drop in DAST-10 scores. Our secondary hypotheses include that intervention group patients receive more referrals at the primary care clinic and during 30 days of follow-up, and both clinicians and patients are more satisfied with the technology-enhanced solution.

Data collection for phase 2 is well underway. We expect to report the data analysis results in early 2018.

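### Primary hypothesis 2 has two conflicting analyses, change from baseline and day-30 means without baseline, and neither is named primary; ASI is in the hypothesis but no test names it

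*Protocol article*

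**What the plan says.** All references are to the protocol article.

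- **Hypotheses.** Hypothesis 2 is about change: less substance use and "a greater drop in Drug Abuse Screening Test (DAST-10) and Addiction Severity Index (ASI) scores within 30 days". The Abstract's Conclusions also include ASI.
- **Hypotheses Testing, opening sentence.** Among other outcomes, it covers "greater reduction in substance use, Student *t* tests will be used".
- **Hypotheses Testing, last paragraph.** "Difference in differences regression tests will be performed on the differences in self-reported substance use amount and frequency and DAST-10 scores", using baseline and 30 days. It then adds: "The correlation coefficients and their confidence levels will be computed". ASI is not mentioned.
- **Power Calculation.** After assuming equal starting levels, it says: "Therefore, to test the hypothesis, we will test the mean substance use levels at 30 days for both arms". The sample size is 86 per arm for a two-sided t test at 5%, 90% power and a medium Cohen effect.
- **Surveys and Table 1.** "The ASI score is a quantitative measure of the user’s substance use". ASI-Lite is scheduled in both arms at the end of the primary care visit and at 30 days. The Table 1 row for substance use is a daily entry in the intervention arm only.
- **Results.** The hypothesis is restated without ASI: "intervention group patients will report a greater reduction in substance use and a greater drop in DAST-10 scores".

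**The concern.** A primary hypothesis needs one outcome and one test, fixed before the arms are compared. Here two sections each say how hypothesis 2 will be tested. One uses the baseline and the other discards it, and nothing says which decides the hypothesis.

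The reason given for discarding it, equal starting levels, is guaranteed by randomization only on average. In any one trial the arms differ somewhat at baseline. The change analysis and the day-30 analysis then give different estimates and can fall on opposite sides of 5%. An analyst who holds both results can choose between them.

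The outcome is loose as well. Amount and frequency of use have no row of their own in Table 1 that covers both arms. ASI is in the hypothesis in two places, absent in a third, and not named in any test. A correlation coefficient does not estimate the difference between arms.

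**Working it through.** **Inputs.** From Power Calculation: two-sided 5%, 90% power, equal arms, medium effect (read as d = 0.5 in day-30 SD units), 86 per arm, 500 in total, up to 20% attrition. Completers: 500 × 0.8 / 2 = 200 per arm. The article gives no correlation ρ between baseline and day 30, so 0.3 to 0.7 is assumed, with 0 as an extreme. Equal SDs at both times are also assumed.

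**1. The plan's own figure.** The noncentral-t solution for d = 0.5 is 85.03 per arm, which rounds up to 86. The stated figure reproduces for the day-30 t test.

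**2. How many distinct analyses?** With two time points and complete pairs, a t test on change and a difference-in-differences model that respects the pairing give the same estimate and test. The conflict is therefore between two analyses, change and day-30 only. (A pooled difference-in-differences regression that ignored pairing would be conservative: simulated type I error 1.9%, 0.5% and 0.05% at ρ = 0.3, 0.5 and 0.7.)

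**3. How far apart are the two estimates?** The day-30 difference minus the difference in change equals the baseline difference between arms. Its standard deviation is √(2/200) = 0.10 SD. The detectable effect of the day-30 test at 90% power is 0.325 SD, so a typical gap is about a third of it (0.10/0.325 = 0.31).

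**4. Type I error if the better result is reported.** Under the null, the correlation between the two estimates is (1−ρ)/√(2(1−ρ)) = √((1−ρ)/2). In 20,000 simulated null trials with 200 per arm:

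| ρ | √((1−ρ)/2) | Tests disagree on significance | Either significant | ANCOVA alone |
|---|---|---|---|---|
| 0.3 | 0.59 | 7.2% | 8.4% | 5.0% |
| 0.5 | 0.50 | 7.9% | 8.9% | 5.0% |
| 0.7 | 0.39 | 8.9% | 9.7% | 5.1% |

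As a check, treating the two test statistics as bivariate normal with that correlation gives 8.8%, 9.1% and 9.4% for either being significant.

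**5. Precision and size.** The variance relative to the day-30 test is 2(1−ρ) for change and 1−ρ² for ANCOVA. Since 1−ρ² = (1−ρ)(1+ρ), the ANCOVA factor never exceeds 2(1−ρ) or 1.

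| ρ | Variance factor: change | Variance factor: ANCOVA | n per arm: change | n per arm: ANCOVA | Power at 200: change | Detectable SD at 200: change | Detectable SD at 200: ANCOVA |
|---|---|---|---|---|---|---|---|
| 0 | 2.00 | 1.00 | 170 | 86 | 0.94 | 0.460 | 0.325 |
| 0.3 | 1.40 | 0.91 | 119 | 78 | 0.99 | 0.384 | 0.310 |
| 0.5 | 1.00 | 0.75 | 86 | 65 | >0.99 | 0.325 | 0.281 |
| 0.7 | 0.60 | 0.51 | 52 | 44 | >0.99 | 0.252 | 0.232 |

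The n columns are for d = 0.5 and 90% power. The stated 86 is too few for a change analysis if ρ is below 0.5 (power 0.79 at ρ = 0.3). It is enough for ANCOVA at every ρ.

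**6. Which baseline?** Under Screening, DAST-10 is taken before the brief intervention but after randomization, on paper in the control arm and on the iPad in the intervention arm. Table 1 marks it optional in the intervention arm only. ASI-Lite is first given at the end of the visit, after the brief intervention.

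**The case against.** The opening sentence of Hypotheses Testing is a loose umbrella. It also puts referral rates under t tests, although the next paragraph gives them a chi-square test. The specific plan for substance use is difference-in-differences, and the day-30 test could be seen as a simplification for sizing, since with equal baselines both target the same expected difference. This has some force, and it is one more reason not to count three analyses. It does not remove the conflict, because Power Calculation states how the hypothesis will be tested, not only how it was sized.

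A valid difference-in-differences analysis is also acceptable in itself, and with 200 completers per arm power is high whichever method is used. That stands: ANCOVA's advantage here is precision and a single fixed answer, not rescue of an underpowered trial.

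On ASI, the general t-test sentence might be stretched to cover it, since Surveys describes ASI as measuring substance use. That is possible, but no analysis names ASI, and Results drops it from the hypothesis. The reference to correlation coefficients may simply be loose wording for regression coefficients, in which case it needs only clarification.

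A reader might also infer that ASI-Lite should become the primary outcome because it covers drug use in the previous month. The document does not settle that. Its first ASI-Lite follows the brief intervention, Results keeps DAST-10 and omits ASI, and the choice belongs to the trial team.

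**Conclusion.** The point holds in this form: hypothesis 2 has two incompatible stated analyses, no designated primary one, and an unsettled outcome list. Choosing between the two after seeing results would raise two-sided type I error from 5% to about 8% to 10%. That range rests on the assumed correlations of 0.3 to 0.7, equal SDs, normal data and 200 completers per arm. It describes what selective reporting would do and is not evidence that it will happen.

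Two stronger readings are not supported. The first is that three different tests compete; the t test on reduction and a paired difference-in-differences coincide. The second is that the trial is too small or its arithmetic wrong; 86 per arm reproduces, and the lowest power found at 200 per arm is 0.94 (change analysis at ρ = 0, d = 0.5).

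**What to change.** 1. Name one primary outcome for hypothesis 2, measured with the same instrument in both arms. The intervention-only daily log cannot serve. Make the other outcomes supportive.
2. Analyse it by ANCOVA of the day-30 value on arm and the baseline value, and report the adjusted mean difference with its 95% CI. This replaces both the difference-in-differences analysis and the day-30 t test. Amend Hypotheses Testing and Power Calculation to match; 86 per arm remains sufficient.
3. Use a baseline taken before the brief intervention. The screening DAST-10 is a candidate, with its difference in mode between arms (paper versus iPad) acknowledged, its optional marking in Table 1 resolved, and its recall period confirmed as suited to 30-day change, since the article does not state it. If the end-of-visit ASI-Lite is the covariate, state the assumption that its past-month items are unaffected by arm.
4. Reconcile ASI across the Abstract, Hypotheses, Hypotheses Testing and Results.
5. Replace the correlation-coefficient sentence with the treatment-effect estimate and its CI.

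**Cost.** The analysis change is wording and needs no extra participants. It should be fixed before any comparison of arms; Results says data collection is under way. If the team decided to change the timing or mode of the baseline, that would be an operational change. The downside is one further model assumption and reliance on a baseline that is comparable between arms.
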